#### Sensitivity Analysis

The following sensitivity analyses will be or can be performed:

Both the primary and secondary analyses will be repeated based on the participants with at least 45 out of 60 (75%) days of data.The change of the secondary outcome will be imputed using the last-observation-carried-forward method if either the corresponding pretest or posttest value is missing.We will conduct the secondary analyses—the effects of message categories and timings—in the RL group.An interaction between the components of the message and time window can be considered in the GEE model for the secondary hypothesis. This interaction term allows us to examine what type of message, sent at what time of the day, leads to the highest increase in daily mood ratings.

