### Measures

For our primary outcomes, we will administer a survey at baseline and at 60-day follow-up, which includes the PHQ-8 [19] and GAD-7 [20]. In addition to these questionnaires, we will also ask open-ended questions to assess how participants are impacted by COVID-19. Questionnaire data will be stored on UC Berkeley’s Qualtrics platform. Our secondary outcome, daily mood ratings, will be collected via text message on a daily basis and stored on the HealthySMS platform. The project coordinator and research assistants will be responsible for managing patient data collection. Once data from all participants are collected, they will be stored on UC Berkeley’s Secure Box, a secure cloud-hosted platform. See Table 1 [21,22] for all included questionnaires and timing of their administration.

**Table 1 table1:** Questionnaires included in the StayWell at Home study and timing of administration.

Questionnaire^a^	Baseline	Follow-up
PHQ-8 (8-item Patient Health Questionnaire)^b^	X^c^	X
GAD-7 (7-item Generalized Anxiety Disorder) scale^b^	X	X
COVID-19 questions	X	X
System Usability Scale^d^	N/A^e^	X

^a^The measures were taken from validated questionnaires in English and Spanish.

^b^The PHQ-8 depression scale and the GAD-7 anxiety scale were not modified.

^c^X indicates that the measure was administered at this time point.

^d^The System Usability Scale [21] was modified to decrease literacy levels, using the Flesch-Kincaid readability test [22].

^e^N/A: not applicable; the measure was not administered at this time point.

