### Statistical Analysis Plan

#### Primary Analysis

Paired *t* tests will be used to detect the improvement in depression score (ie, PHQ-8) and anxiety score (ie, GAD-7) from baseline to follow-up measured 60 days later. Two-sample *t* tests will be used to examine the difference in improvements between the UR and RL groups. The mood ratings of each participant will be collected each day over the 60-day study period. We will also compare the average of daily mood rating improvements compared to baseline (ie, each consecutive daily measure minus the baseline measure) between these two groups using a longitudinal data analysis approach (eg, generalized estimating equation [GEE]). We will not compare the baseline characteristics between the samples in each arm. This practice could potentially be misleading because any differences would be due to chance [26-28].

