#### Secondary Analyses

Using the GEE-based sample size calculation method [31,32] with a small standardized effect size (ie, Cohen *d*=0.2), with the correlation coefficients of 0.2 and 0.4 among the daily mood rating improvements compared to baseline, sample sizes of 84 and 161 are required to detect a group effect for either the UR or RL group, respectively, randomly allocated at baseline. Assuming 15% of the participants will drop out before the end of the study, a sample size of 190 is required for each group.

At a small standardized effect size (ie, Cohen *d*=0.1), with a constant trend of intervention effect over days, sample sizes of 55 and 76 are required to detect the average daily causal effects of message and time window, respectively, for the UR intervention group, using the WCLS-based sample size calculation method proposed by Xu et al under the multilevel MRT design [33]. Assuming each participant has an expected 70% response rate to the sent messages and 15% of the participants are expected drop off before the end of the study, a sample size of 126 is recommended for the UR group. 

Since our primary aim is to detect differences between the UR and RL groups for depression and anxiety scores, we aimed to include at least 128 participants. However, since our goal is also to provide a service during this unprecedented COVID-19 pandemic, we will continue to make the program available and recruit participants until at least April 2021 or for as long as funding allows.

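### The carry-forward rule cannot fill a missing baseline and does not make clear which outcome it covers, and the 45-of-60-day repeat of the RL-UR comparison selects on post-randomisation response instead of testing robustness to missing data

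*Protocol article*

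**What the plan says.** All of this is in the protocol article.

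- **Outcomes (Measures).** PHQ-8 and GAD-7 are primary and have two time points: "For our primary outcomes, we will administer a survey at baseline and at 60-day follow-up". Mood is the secondary outcome: "Our secondary outcome, daily mood ratings, will be collected via text message on a daily basis".
- **Definition of mood change (Statistical Analysis Plan, Primary Analysis).** It is "each consecutive daily measure minus the baseline measure", compared between arms with a longitudinal method such as GEE. PHQ-8 and GAD-7 changes are compared with t tests.
- **Carry-forward (Sensitivity Analysis).** The secondary outcome's change is to be "imputed using the last-observation-carried-forward method if either the corresponding pretest or posttest value is missing".
- **Responder-day subset (Sensitivity Analysis).** "Both the primary and secondary analyses will be repeated based on the participants with at least 45 out of 60 (75%) days of data".
- **Planning rates (Power Analysis, Secondary Analyses).** "Assuming each participant has an expected 70% response rate to the sent messages", together with 15% dropout. Both rates are used there to size the UR group.

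The sensitivity analyses are introduced as ones that will or can be done, so they are partly optional.

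**The concern.** Two of the listed sensitivity analyses bear on missing data. The trial is fully remote and plans for 15% dropout and 30% non-response to messages, so these checks carry the robustness argument.

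The carry-forward rule has two problems. It claims to handle a missing pretest, which carry-forward cannot do. It also attaches two-point language to a daily series, so an analyst cannot tell which outcome is to be imputed, and the two readings behave differently.

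The 45-day repeat covers the primary analyses and therefore the randomised RL-UR comparison. Replying to mood prompts happens after randomisation. The RL algorithm chooses messages in order to raise mood, so replying may depend on arm. A comparison among frequent responders is then no longer a comparison of the groups as randomised. If either analysis agreed with the main result, the agreement could be taken as evidence that missing data do not matter, which neither analysis can show.

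**Working it through.** **1. The plan's own figures.**
- Cut-off: 45/60 = 0.75, as stated.
- Expected rated days at the planned response: 0.70 × 60 = 42, three below the cut-off.
- RL-UR sample size: a two-sample t test at d = 0.5, two-sided 5% (sidedness assumed) and 80% power needs 63.8, so 64 per arm and 128 in total, as stated.
- UR group: 76/(0.70 × 0.85) = 127.7 against the stated 126. This is close enough to confirm that 70% and 15% are the operative planning rates.

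**2. Missing pretest.** Change on day t is the rating on day t minus baseline. Without baseline, every change for that person is undefined. Carry-forward needs an earlier observation, and none exists.

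**3. Which outcome?**

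| Reading | Supported by | Effect on someone who stops |
|---|---|---|
| Daily mood | The words secondary outcome, as defined under Measures | Change held at the last observed value; zero only if there is no later rating or the last rating equals baseline |
| PHQ-8 / GAD-7 | The pretest/posttest wording, which fits a two-point score | Baseline carried to day 60, so change is exactly zero |

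Size under the second reading, for the pre-post change. Take an observed change with mean 0.5 and SD 1, and set 15% of participants to zero:
- Mean: 0.85 × 0.5 = 0.425, a 15% reduction.
- Variance: 0.85 × (1 + 0.25) − 0.425² = 1.0625 − 0.1806 = 0.882, so SD = 0.939.
- Standardised effect: 0.425/0.939 = 0.45.

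The SD must be recomputed because the added zeros change the spread. Holding it at 1 would give 0.425 and overstate the loss.

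**4. Retention under the 45-day rule.** With X the number of rated days out of 60:
- Everyone responds independently at 70%: P(X ≥ 45) = 1 − BinomCDF(44; 60, 0.70) = 0.244.
- Response varies between people (beta-binomial, mean 0.70, ICC assumed):

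| ICC | P(X ≥ 45) | × 0.85 (dropouts never qualify) |
|---|---|---|
| 0 | 0.244 | 0.207 |
| 0.05 | 0.389 | 0.331 |
| 0.1 | 0.438 | 0.373 |
| 0.2 | 0.492 | 0.418 |
| 0.3 | 0.528 | 0.448 |
| 0.5 | 0.584 | 0.496 |

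**5. Consequence for the RL-UR t test.** Of 128 randomised, 128 × 0.207 ≈ 27 to 128 × 0.496 ≈ 63 remain. Two-sample t-test power at d = 0.5 falls from 80% to about 24-50%. Starting from 380 (the 190 per group in the GEE calculation), about 79 to 188 remain and power is about 59-93%. A larger sample restores precision but does not remove the selection.

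**The case against.** The strongest case against has five parts.

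- **Zero change for all dropouts.** A reader might infer that the rule sets every dropout to zero change. The text does not support this: the outcome it names is daily mood, with up to 60 ratings, so the last value is carried. Zero change follows for a missing posttest only if PHQ-8 and GAD-7 are meant. This objection stands, and the 0.45 figure applies only to that reading.
- **Both analyses fail.** A reader might also conclude this. It is too strong for the 45-day subset, which can be run, is labelled a sensitivity analysis and replaces nothing. An average of 70% does not prevent people from reaching 75%, so the cut-off does not contradict the planning rate. This stands.
- **Reach.** Participants join the messaging platform only after completing the baseline survey, so a missing PHQ-8 or GAD-7 pretest should be rare. The article gives no rate of missing baseline mood. The defect in the rule is therefore certain, but how often it would arise is unknown.
- **Scope of the selection argument.** The loss of randomised comparability concerns RL versus UR. The message and timing contrasts are made within the UR group and involve no between-arm comparison. This also stands.
- **Detail belongs in a SAP.** The handling of missing primary outcomes may well be set out in a document not shown, and its absence here is not criticised. The article does fix a method and a threshold, and those can be judged as written.

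The objections do not rescue carry-forward for a missing baseline, the unclear outcome, or the use of the high-responder subset as a check on missing data in the RL-UR comparison.

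**Conclusion.** The point holds in a limited form. The carry-forward rule is defective as written: it cannot be carried out for a missing pretest, and its outcome is ambiguous. Under the mood reading, change is frozen at the last value, and the 45-day subset is the only listed check bearing on missing PHQ-8 and GAD-7. Under the PHQ-8/GAD-7 reading, a missing posttest becomes no change; at the planned 15% dropout the mean change falls by 15% and d goes from 0.50 to about 0.45, assuming the observed participants have d = 0.50.

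The 45-day repeat is feasible, but for RL versus UR it estimates an effect among selected responders. Retention before dropout is about 24% under identical, independent response and 39-58% under ICCs of 0.05-0.5. The ICCs are assumptions, so the range is indicative. Whether response differs by arm is also unknown; the design only makes it possible.

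No primary estimate is overturned. What is weakened is the evidence that those estimates are robust to missing data, so the change should be made but is not critical.

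**What to change.** 1. State which outcome the imputation rule covers.
2. Replace carry-forward for PHQ-8 and GAD-7 with multiple imputation, or a mixed model with baseline means constrained equal across arms, in all randomised participants. Use arm, baseline scores and observed daily mood as predictors or auxiliary variables.
3. Add a delta-adjusted analysis in which dropouts' imputed scores are shifted over a prespecified range, allowed to differ by arm.
4. For daily mood, analyse all observed ratings in the longitudinal model already planned, without freezing values after dropout.
5. Label the 45-day subset a descriptive summary of engaged users, and draw no between-arm inference from it.

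The cost is more analysis code. The predictors are already collected, and no extra participants or assessments are needed. The downside is reliance on a missing-at-random assumption, which the delta-adjusted analysis probes.

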##### Uniform Random Policy

This study design is an MRT [16], where every day during the study treatment, allocation is characterized by a full factorial design with a total of two factors representing supportive *messages* and the *time frame* when the message was sent. The *messages* factor has two levels, and the *time frame* factor has three levels (ie, 9 AM-12 PM, 12 PM-3 PM, and 3 PM-6 PM). Each participant will be rerandomized to a new combination of *messages* and *time frame* every day. The study is set up so that each day participants will be randomized to receive one message out of the message categories (ie, BA vs other skills), constituting a multilevel MRT design with probabilities of 0.5 for the message categories and 0.33 for the timing. Thus, every participant will receive one BA or skill message per day and one mood check-in message.

This design allows us to understand the type and timings of text messages that most improve participants’ mood, which is a secondary aim of this study. MRTs enable the testing of specific intervention components, while still allowing for the evaluation of a causal, average treatment effect of the intervention [16]. Figure 2 shows our MRT design.

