#### Secondary Analysis

For the UR intervention group, the differences in proximal outcome (ie, daily mood rating assessed 3 hours after the message sent) between both message categories (ie, BA versus coping skills) or among the time windows (ie, reference level versus the other three levels) will be examined using the weighted and centered least-squares (WCLS) method for longitudinal data analysis under the multilevel MRT design proposed by Xu et al [24]. This method is similar to the GEE approach. The independent working correlation matrix will be adopted. The covariates include days in study (ie, from 1 to 60 days), day of the week (ie, Monday-Sunday), intervention component (ie, message or time window), and the interaction term between days and intervention component. The trend of the intervention effect over days can be constant, linear, or quadratic. The message or the time window component categories will be converted to dummy variables, and each of these will be centered by the corresponding randomization probabilities (ie, 0.5 and 0.33 for each level of the message and time components, respectively).

The mood rating changes from baseline will be categorized into binary outcomes (ie, high [greater or equal to the median of the whole sample] or low [less than the median]). The WCLS estimator under the MRT design for binary outcome proposed by Qian et al [29] can be applied to the message component (ie, two-level intervention). For the timing (ie, three-level) component, we will propose the novel WCLS method by combining the ideas of both Xu et al [24] and Qian et al [29]. This method can also be extended to model the mood ratings as ordinal outcome variables. 

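### If mood ratings filled by LOCF enter the daily message and timing models, the estimated effects shrink by roughly the share of filled days, even when data are missing completely at random

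*Protocol article*

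**What the plan says.** All places are in the protocol article.

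- **Sensitivity Analysis:** the change in the secondary outcome is to be "imputed using the last-observation-carried-forward method if either the corresponding pretest or posttest value is missing". The model that will use the filled values is not named, and none is excluded.
- **Measures:** the outcome concerned is identified: "Our secondary outcome, daily mood ratings, will be collected via text message on a daily basis".
- **Statistical Analysis Plan, Secondary Analysis:** the proximal outcome for the message and timing effects in the UR arm is the "daily mood rating assessed 3 hours after the message sent". In the WCLS model the treatment dummies are centred: "each of these will be centered by the corresponding randomization probabilities".
- **Uniform Random Policy:** "Each participant will be rerandomized to a new combination of" message and time frame every day, "with probabilities of 0.5 for the message categories and 0.33 for the timing".
- **Statistical Analysis Plan, Primary Analysis:** improvement in mood is defined as "each consecutive daily measure minus the baseline measure".
- **Power Analysis, Secondary Analyses:** the UR arm is sized "Assuming each participant has an expected 70% response rate to the sent messages", with 15% dropout, a standardised effect of 0.1 and a constant effect over days.

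**The concern.** LOCF is usually criticised because its assumption about the missing values may be implausible. Here the problem lies in the design. The effect of interest is that of today's randomised message on mood three hours later. A rating carried from an earlier day was given under that day's category and window, before today's draw was made. Entered as today's outcome, it is credited to a message that cannot have influenced it.

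A sensitivity analysis for missing data should show whether a finding survives nonresponse. This one would reduce a true effect in proportion to the amount filled in, even when nonresponse is harmless and the answered days alone give an unbiased estimate. A real message or timing effect could then be reported as sensitive to missing data. The Discussion intends these results to guide optimisation of the intervention and to serve as preliminary evidence for a just-in-time adaptive intervention.

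**Working it through.** **Inputs from the article:** 60 days; message probability 0.5; window probability 0.33 (taken as 1/3); effect 0.1, constant; response 70%; dropout 15%; 126 UR participants; 80% power; 5% level. **Assumed:** F tests, dropout times, within-person correlation, and missingness completely at random.

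**1. The plan's own sample sizes.** Use a noncentral F test with noncentrality N × 60 × d² × Q.
- Message: Q = 0.5 × 0.5 = 0.25, 1 df. The smallest N is 55 (55 × 60 × 0.01 × 0.25 = 8.25).
- Window: both contrasts at 0.1, Q = 2/9, 2 df. The smallest N is 76 (76 × 60 × 0.01 × 2/9 = 10.13).
- Inflation: 76 / (0.70 × 0.85) = 127.7, against 126 stated.

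The figures 55 and 76 are reproduced exactly and 126 closely, so the effect model below matches the plan's.

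**2. What a filled day contributes.** In the linear model the coefficient is the covariance of the outcome with the centred treatment, divided by the variance of that treatment. On an answered day the covariance is β times that variance. On a filled day the outcome was fixed before today's independent draw, so the covariance is zero. This holds even if earlier messages have lasting effects. Carrying the change rather than the rating makes no difference, because the baseline also precedes today's draw. Hence

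expected LOCF coefficient ≈ β × (answered days / days entering the model).

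**3. Size.**

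| Case | Share answered | Shrinkage |
|---|---|---|
| 70% response, no dropout | 0.70 | 30% |
| 15% dropout, uniform over 60 days, later days filled | 0.70 × (1 − 0.15 × 0.5) = 0.6475 | 35% |
| At least 45 of 60 days answered | at least 45/60 = 0.75 | at most 25% |

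The 30% is approximate. Days before a participant's first answer cannot be filled. On average there are 0.30/0.70 = 0.43 such days, so the share is 42 / (60 − 0.43) = 0.705.

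**4. Simulation.** 126 participants, 60 days, true effects 0.1, correlation 0.4, 1,000 replicates, least squares on centred treatment with participant-clustered variance.

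| Setting | Effect | Answered days: estimate (power) | LOCF: estimate (power) | Ratio |
|---|---|---|---|---|
| No dropout | Message | 0.100 (95%) | 0.071 (86%) | 0.71 |
| No dropout | Window | 0.100 (88%) | 0.071 (72%) | 0.71 |
| Uniform 15% dropout | Message | 0.101 (95%) | 0.066 (81%) | 0.65 |
| Uniform 15% dropout | Window | 0.100 (85%) | 0.066 (67%) | 0.66 |

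Further runs at correlations 0.2 and 0.4 with dropout gave the same estimates to within simulation error. In those runs coverage of the 95% interval under LOCF was 67–70% for message and 74–78% for window, against about 95% on answered days.

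**5. Missing pretest.** With change measured from baseline, the pretest is the baseline rating. No earlier observation exists to carry. Carrying the change score instead does not help, because without a baseline every change for that participant is missing.

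**The case against.** **The model is not named.** The LOCF rule speaks of change, which is the outcome of the UR-versus-RL mood comparison and of the dichotomised analysis. The linear WCLS outcome is described as the rating itself. This stands, and it makes the point conditional. The rule does, however, cover the variable that the message and timing models use, and it excludes neither model.

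**The arm comparison is different.** Arm is fixed for 60 days, so a carried value still belongs to the participant's own arm. This stands. A reader might infer that LOCF dilutes the UR-versus-RL contrast in the same way, but this mechanism does not reach it. The simple factor also does not carry over to the message and timing analyses in the RL arm, where choices depend on past mood.

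**The dropout share is uncertain.** Participants who reply STOP receive no more messages, so their later days may have no category or window to analyse. The 35% figure needs those days to be kept and filled; otherwise the figure is about 30%.

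**LOCF is not the only check.** A reader might infer that the plan's whole examination of missing mood data rests on LOCF. The same section also repeats the analyses in participants with at least 45 of 60 days. LOCF is the only stated imputation, not the only check.

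**Pretest is undefined in that section.** Table 1 lists no baseline mood item, and reading pretest as the previous day's rating would make the rule executable. The definition of change from baseline favours the other reading but does not settle it.

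**The consequence is limited.** The section introduces these as analyses that will or can be done, and the bias is toward the null. This stands and bears on the weight of the point, not on the mechanism.

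**Conclusion.** The point holds in conditional form. If LOCF-filled days enter the UR-arm linear WCLS model, the message and timing effects shrink toward zero by roughly the share of filled days: about 30% at the planned response rate, about 35% with filled days after uniform dropout, and at most about 25% in the 45-of-60-days subset. These figures assume missingness completely at random, a constant effect and the plan's 70% and 15%; other rates change them in proportion.

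A reader might infer that the trial's main findings are biased. The documents do not support that: LOCF appears only as a sensitivity analysis, so neither the main WCLS estimate nor the PHQ-8 and GAD-7 tests are affected. The harm is that a supportive analysis could make a real effect look fragile. Separately, if pretest means baseline, LOCF cannot fill it. The rule should be changed, but it does not threaten the trial's primary conclusions.

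**What to change.** - Do not use LOCF for daily mood in the message and timing models. Leave unanswered days missing.
- If an imputed sensitivity analysis is wanted, use multiple imputation. The imputation model should contain that day's randomised category and window, study day, weekday and the participant's other ratings, so that an imputed day keeps its link to its own message.
- Remove the LOCF rule for a missing pretest.

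The cost is one bullet in the plan and some programming. No new data are needed.
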